### Procedure

All data are collected at a baseline research visit, prior to the patients starting treatment in the service. These visits take place at the NIHR/Wellcome Trust King’s Clinical Research Facility. This visit involves a diagnostic interview carried out with a trained researcher, collection of biological samples (hair and blood), and completion of a range of questionnaires. Outcome measures will be collected in everyday contact with IAPT staff as part of routine IAPT practice at each treatment session and will be available on the IAPT patient record system. These variables are described below.

### Measures

#### **
*Predictor variables*
**

The final choice of clinical and psychological predictors was based on discussions over a series of meetings with a large multidisciplinary group of academic experts, a systematic review of the literature conducted by the project coordinator (NG) and discussion over 3 subsequent meetings with the core Steering Committee who are all co-authors of this paper. The final list, which was reached by group consensus, has been considered comprehensive while at the same time manageable within a target completion time of 90 minutes for the whole assessment. This was judged to be the maximum time that we could impose on participants. Pilot work with the interview has confirmed that this is a realistic estimate of the time needed for completion.

PROMPT is collecting biological data as part of the National Institute for Health Research (NIHR) BioResource for Mental Health, which aims to enrol and collect biological samples from 52,000 healthy volunteers, patients and relatives. For PROMPT, this includes blood processed for DNA, RNA, buffy coat, serum and plasma. This sampling protocol allows for testing of an extensive battery of biomarkers relevant to treatment response in psychiatric disorders, and which are being routinely tested in a number of ongoing studies on a range of diagnostic categories. The BioResource project has separate ethical approval for the collection, storage and analysis of biological samples.

Demographic and patient characteristics are shown in Table 1. Table 2 shows the predictor variables, which will be collected at the baseline interview.

**Table 1 T1:** Demographic and treatment factors

**Demographics**	
Socio-economic status	Current medication
Ethnicity	Physical health
Age	Benefits status
Working status	Marital status

**Table 2 T2:** Predictor variables

**Predictors**	**Measure**	**Reference**
Biological sampling	Blood, saliva, hair	N/A
Diagnosis	MINI	[9]
Personality disorder	SAPAS	[10]
	SCID-II	[11]
Hypomania	Hypomania Checklist	[12]
Previous treatments and psychiatric history	Maudsley Staging Model	[13]
Social support	Oslo 3 Social Support Scale	[14]
Self-criticism	Forms of Self Criticising and Self Reassuring Scale (FSCRS)	[15]
Stressful life events	List of Threatening Experiences	[16]
Childhood abuse	Childhood Trauma Questionnaire	[17]
Quality of life	EQ-5D	[18]
Illness perceptions	Brief Illness Perceptions Questionnaire	[19]
Self-efficacy	General Self-efficacy Scale	[20]
Alcohol	AUDIT	[21]
Drug use	Drug abuse/dependence subscale - PDSQ	[22]

#### **
*Diagnosis*
**

The Mini International Neuropsychiatric Interview (MINI) is used to assess diagnosis of participants in this project. The MINI is a structured interview which assesses DSM diagnoses, and is rapid to administer. The MINI covers the following diagnoses: Major Depressive Episode (MDE); recurrent MDE; MDE with melancholic features; dysthymia; suicidality; mania and hypomania; panic disorder; social phobia; agoraphobia; obsessive compulsive disorder; post traumatic stress disorder; alcohol abuse; alcohol dependence; substance use; substance dependence; psychotic disorders; mood disorder with psychotic features; anorexia; bulimia; generalised anxiety disorder; and antisocial personality disorder. The MINI has good internal reliability and consistency [9].

#### **
*Personality disorder*
**

All participants complete the Standardised Assessment of Personality – Abbreviated Scale (SAPAS) [10], an eight item screen for personality disorder. Each item is rated as yes or no, giving a maximum score of eight. In clinical populations, a cut-off three is suggested for identification of cases at high risk of personality disorder. The SAPAS has acceptable internal consistency (Cronbach’s alpha = 0.68). Participants will also complete the borderline personality subsection of the Structured Clinical Interview for DSM-IV Personality Disorders (SCID-II; [11]). The SCID-II is a semi-structured interview delivered by a trained member of the research team to assess presence of anti-social personality disorder and borderline personality disorder. Questions are rated as 1 “absent”, 2 “sub-threshold” or 3 “threshold”. The SCID-II demonstrated acceptable test-retest reliability (kappa = 0.68) as well as acceptable inter-rater reliability (kappa = 0.68) in previous studies.

#### **
*Hypomanic symptoms*
**

The Hypomania Checklist (HCL-16) is used to screen for the presence of hypomanic symptoms to aid in the diagnosis of bipolar disorders [12]. The HCL-16 has been developed from the original HCL-32 and studies have supported the reliability and validity of this shorter measure [12]. Each item is rated as either “yes, present or typical of me” or “no, not present or not typical of me”. There is support for a two factor structure for this scale, the first a ‘active-elated’ factor and the second a ‘risk-taking/irritable’ factor. Reliability for these two subscales and the total score are within acceptable levels (Cronbach’s alphas 0.65-0.77).

#### **
*Previous treatments*
**

Information will be collected about the number of previous episodes each patient has experienced, duration of previous episodes, their previous history of psychological or pharmacological treatment and the age of onset. Current prescribed medication will also be recorded, including type of drug, number of doses per day and dosage. Treatment resistance will be quantified using a modified version of the Maudsley Staging Model [13].

#### **
*Social support*
**

Social support is measured using the three-item Oslo Social Support scale (OSS-3) [14]. The first question measures how many people the participant is close to, with response options ranging from none to more than five. The second question asks the participant to rate how much of an interest other people take in the participant’s life. The third question asks participants to rate if they could get practical help from their neighbours, with responses ranging from very easy to very difficult.

#### **
*Self-critical thoughts*
**

Participants complete the Forms of Self-critical/Attacking and Self-reassuring Scale (FSCRS) [15]. This is a 23-item measure eliciting a score for self critical thinking and self-reassuring thoughts. The self-critical subscale is divided in to hated self, inadequate self, and reassured self. Items are rated using a Likert scale ranging from 0 “not at all like me” to 4 “extremely like me”. The three subscales have good internal consistency with Cronbach’s alphas of 0.86-0.90 [15]. A recent study has supported the three factor structure of this scale [23].

#### **
*Life events*
**

Stressful life events are assessed using the List of Threatening Events Questionnaire [16], a 12-item measure which includes negative events such as serious illness, death, unemployment and loss of an important relationship. Participants mark whether the event has happened to them, and if it has, the date that it occurred. The scale has good test-retest reliability for most items (kappa = 0.78 – 1.0) with the exception of the question relating to having an item stolen, which has lower reliability (kappa = 0.24). There is also good agreement between individual participants and others (kappa = 0.7 - 0.9) and good agreement with interview based measures (sensitivity = 89%, specificity = 74%).

#### **
*Childhood trauma*
**

Traumatic events during childhood are measured using the Childhood Trauma Questionnaire, a 28-item measure that covers five domains. These are: emotional abuse, physical abuse, sexual abuse, emotional neglect, and physical neglect. Questions include “people in my family hit me so hard that it left bruises or marks” (emotional abuse). Each item is rated on a five point Likert scale from “never true” to “very often true”, with scores for each sub scale ranging from 5-25, and the total score from 25-125. The subscales have good internal consistency with Cronbach’s alphas ranging from 0.61 – 0.92) [17].

#### **
*Quality of life*
**

Quality of life is measured using the EuroQol (EQ-5D) [18] which consists of a five part questionnaire and one visual analogue rating scale. The five questions cover self-care, pain, mood, mobility and usual activities and are answered on a three-point Likert scale, ranging from no problems to extreme problems. The visual analogue scale asks participants to indicate how they would rate their health overall today, on a scale from 0 “worst health imaginable” to 100 “best health imaginable”.

#### **
*Illness perceptions*
**

Beliefs about illness are assessed using the nine-item Brief Illness Perceptions Questionnaire [19]. Five questions assess cognitive representations of illness, two assess emotional representations and one assesses illness comprehension. These questions are rated from 0 to 10. The final question asks respondents to list three factors they consider had a causal role in their illness. The original questionnaire contains the term “illness” but this has been changed to “depression/anxiety” for the current project.

#### **
*Self-efficacy*
**

Self-efficacy is measured using the General Self-efficacy Scale [20]. This is a ten item measure which is rated from 1 “not at all” to 4 “exactly true” and is designed to assess respondents beliefs in their ability to complete tasks. The scale has been shown to have good reliability across a variety of participant groups (Cronbach’s alpha ranging from 0.76-0.90).

#### **
*Alcohol*
**

Alcohol consumption is assessed using the 10-item Alcohol Use Disorders Identification Test (AUDIT). The questions in this scale measure alcohol consumption, dependence and problems related to alcohol use. For example, questions include “How often during the last year have you failed to do something that was expected of you because of drinking?” Items have different response categories but each are scored from 0 – 4, giving a possible range of 0 – 40. A score of above eight is indicative of a problem with drinking [21]. A review paper including 18 studies using the AUDIT reported that internal consistency is reliably reported to be above 0.80 [24].

#### **
*Drug use*
**

Drug use is assessed using the drug use/dependency subscale of the Patient Diagnostic Screening Questionnaire [22]. This is a six item measure with response options of yes or no. Questions include “(during the past two weeks) did you think you had a drug problem?”.

#### **
*Outcome measures*
**

The primary outcome for PROMPT will be symptom change for depression and anxiety, as measured nationally by IAPT using by the PHQ-9 (Patient Health Questionnaire) and GAD-7 (Generalised Anxiety Disorder assessment) [25,26]. The PHQ-9 is a self-administered scale covering nine symptoms of depression, which are rated from 0 “not at all” to 3 “nearly every day”. With a sample of patients from primary care, the scale was found to have good reliability (Cronbach’s alpha = 0.89) and sensitivity and specificity of 88% [25]. The GAD-7 is a seven item self report measure, rated from 0 “not at all” to 3 “nearly every day”. The scale has good reliability (Cronbach’s alpha = 0.92) and sensitivity of 89% and specificity of 82% [26].

Both these measures are routinely collected as part of standard IAPT practice at every treatment session. Data will be gathered from the IAPT patient records system (IAPTus) with prior consent of participants. A score of 10 or more on the PHQ-9, and a score of 8 or more on the GAD-7 indicates caseness [25,26]. Participants who score above these thresholds for caseness on both the PHQ-9 and GAD-7 at their final appointment, will be defined as being in the ‘non-recovered’ group. The standard IAPT measure of Reliable Change Index will also be used as an outcome measure of treatment response which will be based on a drop of 6 points for the PHQ-9 and a drop of 5 points for the GAD-7 [27].

Secondary outcomes will be employment status, benefits status, engagement with services, and work and social functioning. Employment and benefits data is routinely collected at each IAPT appointment and entered on to the patient records system. Measures of engagement with IAPT services will include failure to engage, drop-out or discharge. Work and social functioning is measured using the Work and Social Adjustment Scale, a five item self-report measure collected as part of the routine IAPT outcome measures. This information will be collected from the care pathway of the patient records system IAPTus, which is routinely updated by IAPT clinical and admin staff.

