## Background

Depression and anxiety within the general population are a continuing and significant public health problem [1]. The Adult Psychiatric Morbidity Survey showed that 16% of adults overall met the criteria for at least one common mental health disorder (defined in this survey as depression and/or anxiety disorders) [2]. Suffering from depression and/or anxiety has a significant impact on an individual’s life, including increased mortality [3], reduced quality of life [4] and reduced attendance and productivity at work [5]. The Improving Access to Psychological Therapies (IAPT) service was developed to provide psychological treatment for people with these common mental health disorders in order to address the high prevalence and burden of these disorders, and the problem that many people are untreated.

The therapeutic approaches used by IAPT are recommended as first-line treatment for mild to moderate depression and anxiety, in some cases along with appropriate medication, by the National Institute for Clinical Excellence [6]. IAPT services use a standardised protocol and collect considerable amounts of outcome data. This provides an opportunity for researchers to collect data on large populations (3000 per year in some services) of people with common mental health disorders undergoing similar treatments. Recently, the IAPT programme has reported early successes over its first three years, notably the treatment of “the first million patients” [7]. Overall recovery rates, defined as moving from caseness to non-caseness on measures of low mood and anxiety, were 45% in the last quarter of 2011/12, demonstrating consistent improvement over the duration of the programme and progression towards the original target of 50% [7].

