Whilst these recovery rates are encouraging, they also show that around half of patients are not meeting standard definitions of recovery at the end of their treatments. Further, it is likely that a substantial proportion of those who do recover then go on to relapse in due course. Our knowledge of predictors of treatment response for depression and anxiety, both in terms of psychological and pharmacological treatments, is limited. It is likely that depression and anxiety disorders have many and varied causes, across psychological, social, and biological factors. Only by studying large cohorts of patients receiving treatments will it be possible to identify factors that predict positive or negative response and, by understanding these, develop new targets for treatment.

The aim of this project is therefore to provide an infrastructure to understand the predictors of treatment response, and to allow recruitment and follow up of subgroups of participants who do not respond to treatment in order to devise experimental studies to identify new treatments (both psychological and pharmacological). The project is supported by the SLaM Biomedical Research Centre which aims to provide infrastructure support for experimental medicine studies, and phase 1 and 2 trials.

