### Participants

Participants are recruited from one IAPT service provided by South London and Maudsley NHS Foundation Trust (SLaM). Inclusion criteria for this project are that patients are accepted by the IAPT service for treatment, and that they are able to give informed consent. Patients are excluded if they are not sufficiently fluent in English.

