### Sample size

This is a naturalistic, observational project and therefore our sample size estimates are based on patient throughput and human resources. Based on these factors, we estimate to recruit up to 600 patients at baseline in the first year of the project. Using existing drop-out rates from SLaM IAPT services, we expect a drop-out rate of approximately 28%, leaving us with a sample of 472. According to power calculations, with power set at 0.8 and alpha at 0.05, this will allow us to detect standardised effect sizes of 0.13 in linear regression models estimating the effects of baseline factors in recovery. This is considered to be clinically significant; for example, a recent study of predictors of recovery [8] in the same setting showed that baseline PHQ-9 and GAD-7 scores were independently associated with recovery rates in a multiple regression model, with effect sizes ranging 0.14-0.21.

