### Analysis

Descriptive summaries of socio-demographic information will be provided for baseline, and follow up time-points for the sample as appropriate. Descriptive summaries at the level of IAPT services will also be provided. Missing data will be reported for all treatment time-points to describe retention/drop-out rates. Reasons for drop-out will be recorded. We will use the STROBE statement (http://www.strobe-statement.org/index.php?id = available-checklists) for a list of items to be reported. All statistical analyses will be carried out in the statistical software package STATA. Descriptive summaries for all outcome measures will be provided. Continuous outcome measures will be inspected visually to assess the normality of data and to check for outliers. Univariate associations with IAPT non-recovery will be explored using t-tests (for normally distributed data) and Mann-Whitney tests (for skewed data). The independence of associations between the proposed predictor variables and IAPT non-response will be explored using linear mixed model methods (for continuous outcome measures) and logistic regression (for categorically-defined outcomes i.e. recovered vs. non-recovered). The possibility of sex interactions and non-linear effects will be examined. Analysis of residuals from the model will be performed to assess the model fit and to check for outliers.

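### Non-recovery is defined as caseness on both PHQ-9 and GAD-7, which conflicts with the article's own account of IAPT recovery and leaves participants who are still cases on one scale counted as recovered or in no group

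*Protocol article*

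**What the plan says.** All references are to the protocol article.

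- **Measures, Outcome measures.** Caseness is defined first: "A score of 10 or more on the PHQ-9, and a score of 8 or more on the GAD-7 indicates caseness". The non-recovered group is then made up of "Participants who score above these thresholds for caseness on both the PHQ-9 and GAD-7 at their final appointment". The section names symptom change on the two scales as the primary outcome and adds the Reliable Change Index as a further measure of response.
- **Background.** The national benchmark reads "Overall recovery rates, defined as moving from caseness to non-caseness on measures of low mood and anxiety, were 45" per cent. The next paragraph draws the motivation for the study from it: "around half of patients are not meeting standard definitions of recovery at the end of their treatments".
- **Analysis.** The univariate step is "Univariate associations with IAPT non-recovery will be explored using t-tests" or Mann-Whitney tests. The model for the binary outcome is "logistic regression (for categorically-defined outcomes i.e. recovered vs. non-recovered".
- **Participants.** "Inclusion criteria for this project are that patients are accepted by the IAPT service for treatment", together with capacity to consent. No caseness at entry is required.

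The article gives no separate definition of recovered and no third category.

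**The concern.** If recovery means non-caseness on low mood and on anxiety, its complement is caseness on at least one of them. The outcome definition attaches the word both to the wrong side: it requires both conditions for non-recovery, where the Background's account implies both for recovery.

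Participants who finish as a case on exactly one scale are then either placed with the recovered or left out of the comparison without notice. In the first case the reference group mixes people who are well with people who are still ill, and the predictors found are those of persisting depression and anxiety together. In the second case the model is fitted to the two extremes only. Either way the result is not what the Analysis section calls it, and the recovery rate cannot be set beside the 45% that motivates the study.

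**Working it through.** **Logical check.** Let D mean a final PHQ-9 of 10 or more, and A a final GAD-7 of 8 or more.

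| Final status | Background's account of recovery | Outcome measures rule |
|---|---|---|
| neither D nor A | recovered | not in the non-recovered group |
| D only (e.g. PHQ-9 24, GAD-7 7) | not recovered | not in the non-recovered group |
| A only (e.g. PHQ-9 9, GAD-7 21) | not recovered | not in the non-recovered group |
| D and A | not recovered | non-recovered |

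The two definitions differ in the second and third rows. Since the logistic model contrasts two groups only, those rows go to recovered by inference, or to neither group.

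The same definition has two smaller faults:

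- Non-recovery requires a score above the thresholds, while caseness includes scores of exactly 10 or 8. Read literally, a participant at exactly 10 and 8 is a case on both scales but not non-recovered.
- The Background's recovery is a move out of caseness, but neither the inclusion criteria nor the outcome rule requires caseness at baseline.

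**Size, as an illustration.** The article states no figure that depends on this rule, so there is nothing to reproduce.

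Inputs:
- P(below both thresholds) = 0.45, from the Background, so P(case on at least one) = 0.55.
- Equal marginal caseness p on the two scales, bivariate normal final scores, and correlation r from 0.6 to 0.9. These are assumptions and are not in the article.

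Formulas: solve for the common cut-off c with Φ₂(c, c; r) = 0.45. Then
- p = 1 − Φ(c)
- case on both = 2p − 0.55
- case on exactly one = 0.55 − case on both
- share of the recovered group still a case = exactly one / (1 − both)

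| r | p | both | exactly one | share of recovered still a case |
|---|---|---|---|---|
| 0.6 | 0.407 | 0.264 | 0.286 | 0.286/0.736 = 39% |
| 0.7 | 0.426 | 0.301 | 0.249 | 0.249/0.699 = 36% |
| 0.8 | 0.448 | 0.347 | 0.203 | 0.203/0.653 = 31% |
| 0.9 | 0.478 | 0.407 | 0.143 | 0.143/0.593 = 24% |

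(Computed unrounded, so the last digit may differ if reworked from the table.)

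The non-recovered share under the written rule is thus 26% to 41%, against 55% under an either-scale rule.

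In numbers of participants, the Sample size section says "we expect a drop-out rate of approximately 28%, leaving us with a sample of 472", but 600 × 0.72 = 432. Exactly-one cases number about 135 to 68 of 472, or 124 to 62 of 432.

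**Sensitivity.** With 50% below both thresholds in place of 45%, exactly-one cases are 28% to 14% of participants, and 36% to 22% of the recovered group are still cases. With the 45% kept and r = 0.7, moving one cut-off 0.5 SD above the other raises exactly-one cases from 25% to 29%, so the equal-marginals assumption does not inflate the result.

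**The case against.** - **The Background sentence reports a national statistic and is not this study's outcome definition; it also does not say outright that caseness on one scale rules out recovery.** True, but that is its natural reading. The link to this study comes from the Analysis section, which calls the outcome IAPT non-recovery, and from the Background's appeal to standard definitions. If persistent caseness on both scales were the deliberate target, it would need its own name, and nothing in the article says that it is.
- **That one-scale cases are analysed as recovered is inferred.** This stands. It follows from the two-group contrast and is not stated. The only alternative is that they have no group, which is also a defect.
- **The primary outcome is symptom change, and the Reliable Change Index is used as well.** This stands as a limit on the damage. Neither depends on the both-scales rule, so most of the outcome set is sound. Neither repairs the recovered versus non-recovered contrast, which is the only categorical outcome that the Analysis section names.
- **The percentages rest on assumptions.** This stands. The correlation and marginals are assumed. The 45% refers to people who moved out of caseness, whereas this cohort has no entry caseness requirement. Fixing 55% as cases on at least one scale also presupposes the either-scale reading. The number classified may exceed 432, because the Discussion plans to use the last session attended.

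Two stronger readings are tempting but not supported. A reader might infer that someone with depression alone or anxiety alone can never be non-recovered. The rule uses final scores only, so such a person is non-recovered if both scales are over threshold at the end. A reader might also infer that selection for follow-on studies (objective 5) misses these participants. The article does not say that selection uses this group.

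**Conclusion.** The definition is wrong as written. It conflicts with the Background's account of IAPT recovery and with the label used in the Analysis section, and that conflict does not depend on any assumed number. Participants who remain a case on one scale are by inference analysed as recovered, or else have no category, and the binary predictor analysis is biased towards persistent comorbid caseness.

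Under the stated assumptions about one participant in seven (14%, correlation 0.9) to more than one in four (29%, correlation 0.6) is affected, and 24% to 39% of the recovered group would still be cases. These figures show plausible size and are not estimates for this cohort. The fault is confined to the binary outcome and does not extend to symptom change or the Reliable Change Index.

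**What to change.** In Outcome measures:

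1. Define non-recovered as a PHQ-9 of 10 or more, or a GAD-7 of 8 or more, at the final appointment, and recovered as below both thresholds. Writing at or above threshold also removes the clash over scores of exactly 10 or 8.
2. Restrict the recovery analysis, or at least any comparison with the 45%, to participants who were cases on at least one scale at baseline. Changing both to either is not enough alone, because participants who were never cases would still count as recovered.
3. If case on both scales is of interest, report it only as a separately named secondary category, such as persistent comorbid caseness.

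Cost: a few sentences and no new data, since both scales are recorded at every session. The reported recovery rate will be less favourable, and the baseline restriction makes the denominator slightly smaller.
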